## Abstract

**Background::**

Hepatocellular carcinoma (HCC) is a complicated condition influenced by multiple confounding factors, making optimum patient management extremely challenging. Ethnicity, stage at diagnosis, comorbidities and tumour morphology affect outcomes and vary from region to region, and there is no common language to assess patient prognosis and make treatment recommendations. Despite recent efforts to reduce the incidence of HCC, most patients present with unresectable disease. Non-surgical treatments include ablation, transarterial chemoembolisation and the multikinase inhibitor, sorafenib, but their effects in all patient subgroups are not known and further information is needed to optimise the use of these treatments.

**Aims::**

The Global Investigation of Therapeutic DEcisions in Hepatocellular Carcinoma and Of its Treatment with SorafeNib (GIDEON) study (ClinicalTrials.gov identifier NCT00812175; http://clinicaltrials.gov/) is an ongoing global, prospective, non-interventional study of patients with unresectable HCC who are eligible for systemic therapy and for whom the decision has been taken to treat with sorafenib under real-life practice conditions. The aim of this study is to evaluate the safety and efficacy of sorafenib in different subgroups, especially Child-Pugh B where data are limited.

**Discussion::**

This study will recruit 3000 patients from > 40 countries and follow them for approximately 5 years to compile a large and robust database of information that will be used to analyse local, regional and global differences in baseline characteristics, disease aetiology, treatment practice patterns and treatment outcomes, with a view to improve the knowledge base used to guide physician treatment decisions and to improve patient outcomes.

What's knownHCC is a complex disease influenced by multiple confounding factors that vary from region to region, making optimum patient management extremely complex.Sorafenib is an oral multikinase inhibitor with proven efficacy in patients with unresectable HCC, but data in Child-Pugh B are limited.There is a need to fully evaluate existing treatments in all patient subgroups to optimise their use.What's newGIDEON will generate data from 3000 patients to evaluate the effects of sorafenib in different patient subgroups, and the resulting large database will be used to analyse local, regional and global differences that influence patient prognosis and management, with a view to refine HCC staging and evaluation and better inform treatment decisions

## Introduction

Hepatocellular carcinoma (HCC) is the sixth most common cancer worldwide, but because of the poor prognosis associated with this disease, it is the third most common cause of cancer-related death (1). Over 80% of patients with HCC are in developing countries, with particularly high incidence rates in sub-Saharan Africa and Southeast Asia (1). There is a low incidence of HCC in developed countries such as the USA, Australia and the UK, but these rates are rising (2).

Risk factors for the development of HCC have been well documented and include the presence of cirrhosis, infection with hepatitis B and C viruses, heavy alcohol intake, diabetes and obesity (1,2). Although surveillance and vaccination programmes have reduced the incidence of HCC in certain populations (3,4), the majority of patients still present with unresectable disease and are unsuitable for surgery. Current treatments for unresectable disease include loco-regional interventions and systemic therapies, although further data on all treatments are required to fully understand their potential, e.g. in patient groups not included in clinical trials.

Non-surgical loco-regional treatment options include ablation therapy and transarterial chemoembolisation (TACE). Ablation therapy is associated with a 5-year survival rate of 40–70%, with best responses seen among patients with single tumours and preserved liver function (5). However, TACE is recommended for patients with large/multifocal tumours with no vascular invasion or extra-hepatic spread and is associated with objective response rates of 16–60% (3). Although survival benefits have been reported in only two randomised controlled trials (RCTs) (6,7), a robust meta analysis showed that the treatment with TACE was associated with significant improvements in 2-year survival vs. control (8). However, TACE treatment has a number of important limitations. Residual tumour growth following treatment means that treatment repetition is necessary. Additionally, many of the clinical studies investigating TACE have used a wide range of treatment strategies, including different types of embolic particle, chemotherapy, emulsifying agent and numbers of treatment sessions. For this reason, there is no clear evidence to support an optimum treatment strategy (9). Also, TACE therapy is only possible in patients where the arterial blood supply to the tumour can be isolated, and is not recommended in patients with portal vein thrombosis, those with Child-Pugh C liver function or those with a total serum bilirubin level > 3 mg/ml, as all of these factors have been identified as predictors of poor prognosis in patients treated with TACE (9). Finally, treatment with TACE is associated with considerable side effects; the most commonly reported being postembolisation syndrome that occurs in > 50% of treated patients (3). Other less frequent but more serious complications include hepatic abscess and cholecystitis. Further research is therefore needed to optimise TACE treatment strategy and ensure treatment efforts are directed at patients who will most likely benefit.

Systemic therapies investigated for unresectable HCC have included single-agent and combination chemotherapy regimens, but their efficacy has been disappointing and their use is no longer recommended (9). More recently, the Sorafenib HCC Assessment Randomized Protocol trial, a multicentre, Phase III, double-blind, placebo-controlled trial of 602 Western patients with unresectable HCC, showed that treatment with the oral multikinase inhibitor, sorafenib (Nexavar®; Onyx Pharmaceuticals, Inc., Emeryville, CA, USA; Bayer HealthCare Pharmaceuticals, Inc., Wayne, NJ, USA; Bayer Schering Pharma AG, Berlin, Germany), was associated with a significant improvement in survival compared with placebo [median overall survival (OS) of 10.7 months vs. 7.9 months for sorafenib and placebo respectively, p < 0.001] (10). As a result, sorafenib is the first systemic anticancer therapy indicated for treating these patients (9). Similar benefits (median OS of 6.5 months vs. 4.2 months for sorafenib and placebo respectively, p = 0.014) were reported in a Phase III, randomised, double-blind, placebo-controlled trial of 226 patients with unresectable HCC from the Asia-Pacific region, thus confirming the efficacy of sorafenib in a broad geographic patient population (11). However, all patients included in these two large RCTs had preserved liver function (Child-Pugh A), and our knowledge regarding the efficacy of sorafenib in patients with hepatic impairment is limited to small subgroups of patients from Phase I and II studies (12,13). Further studies to evaluate the efficacy of sorafenib among all patient groups are therefore needed.

Current treatment guidelines for unresectable disease are therefore based on the best available evidence, including non-randomised trials, case studies and expert opinion; however, significant data gaps exist. Further evidence is needed to fully evaluate current treatment options and optimise their use to improve patient outcomes.

Against this background, the Global Investigation of Therapeutic DEcisions in Hepatocellular Carcinoma and Of its Treatment with SorafeNib (GIDEON) study is an ongoing global, non-interventional study (NIS) of patients with unresectable HCC who are to receive sorafenib as part of their standard clinical care. The study should produce the largest, most robust database of information on factors influencing treatment and outcome of patients with HCC. This manuscript will include details of the GIDEON aims and objectives, study design, target recruitment and timeline. It will also describe the planned analyses and discuss how it is hoped that findings from this study will allow us to gain a detailed understanding of the factors that influence the prognosis and management of these patients, and how this in turn will help us to refine HCC staging and evaluation, better inform treatment choices and ultimately improve outcomes for patients with HCC.

## The GIDEON study

### Aims, objectives and rationale for GIDEON

Non-interventional studies, or observational studies, are postauthorisation safety studies (PASS) that are usually conducted to gain further information about a licensed product. Observational studies are characterised by the fact that assignment to a particular therapy strategy is not mandated by a study protocol but reflects the participating physician’s current practice. The physician alone decides which treatment, if any, is appropriate. In NIS, the decision to include a patient in a study is separate from the treatment decision. Furthermore, no additional diagnostic or monitoring interventions are mandated for the patient as a result of inclusion in an NIS. NIS serve a wide range of purposes but are of particular value in providing information in wider populations or subgroups not covered in RCTs (14). NIS also enable information to be gathered on other parameters not usually assessed in the clinical trial setting, such as patient acceptance and compliance, physician adherence to information and directions for use and prescription behaviour. The importance of NIS in the literature is increasingly recognised, and guidelines were developed to improve the analysis and reporting of observational studies (15). NIS provide opportunities to enhance the evidence base for established drugs and therapies and increase understanding of the impact of treatments in real-world practice (14).

GIDEON is a global, prospective NIS of patients with unresectable HCC who are candidates for systemic therapy and for whom the decision has been taken to treat with sorafenib. It was initiated to fulfil the postapproval commitment to organisations such as the European Medicines Agency to gather data on the safety and efficacy of sorafenib in patients with Child-Pugh B liver function. Additional goals are to compile a large and robust database of HCC treatment patterns and outcomes among patients with unresectable disease who are candidates for systemic therapy, to answer clinically relevant questions and gain a better understanding of the safety of sorafenib with loco-regional therapies, given either concomitantly or sequentially. Data will also be gathered in the USA and possibly other regions on the characteristics, disease course and treatment outcomes of patients with newly diagnosed HCC or recurring disease after curative treatments, who are not candidates for systemic therapy with sorafenib.

Based on these goals, the primary objective of GIDEON is to evaluate the safety of sorafenib in patients with unresectable HCC in real-life practice conditions. Secondary objectives are to: evaluate the efficacy [OS, progression-free survival (PFS), time to progression (TTP), response rate and stable disease rate] of sorafenib in these patients; determine the duration of therapy according to various patient characteristics; evaluate methods of patient evaluation, diagnosis and follow-up; assess comorbidities and their influence on treatment and outcome in real-life practice rather than a controlled clinical trial setting and evaluate the practice patterns of the physicians involved in the care of these patients.

This study was conducted according to established regulations and recommendations relating to the conduct of NIS; volume 9A of the Rules Governing Medicinal Products in the European Union (16). When required, documented approval from the appropriate ethics committee(s)/institutional review board was obtained for all participating centres prior to the study, according to Good Clinical Practice and local laws, regulations and organisations.

### Establishing a global NIS

GIDEON is a Phase IV, international, prospective, open-label, multicentre, non-interventional PASS of patients with unresectable HCC receiving sorafenib under real-life conditions. Approximately, 3000 eligible patients will be recruited by participating physicians from > 40 countries across Europe, Latin America and the Asia-Pacific region and from the USA (Figure 1) and will be observed from the start of sorafenib therapy to patient withdrawal, loss to follow-up, death or final visit.

**Figure 1 fig01:**
[figure not shown]
The global reach of GIDEON

An overview of the GIDEON timeline and planned analyses is shown in Figure 2. The first patient’s first visit was recorded in January 2009 and the last patient’s first visit is anticipated to occur in quarter four of 2012. Interim analyses for safety will be conducted after 500 and 1500 patients have been recruited and followed for 4 months, with the final analysis anticipated in quarter two or three of 2014. The study will end 12 months after enrolment of the 3000th eligible patient, irrespective of whether the final patient dies or not, is lost to follow-up or survives.

**Figure 2 fig02:**
[figure not shown]
An overview of the GIDEON timeline and planned analyses

### Patients to be included in GIDEON

Patients with histologically or cytologically documented or radiographically diagnosed unresectable HCC who are candidates for systemic therapy, and for whom a decision has been made to treat with sorafenib, are eligible for inclusion in GIDEON if they have a life expectancy of > 8 weeks and have provided signed informed consent. Patient exclusion criteria are based on the approved local product information for sorafenib.

### Data collection

All data will be collected using case report forms (CRFs). These will be available as paper and electronic versions, with participating countries and their sites able to choose the format of preference. Data will be collected from all enrolled patients at study entry and start of sorafenib, then at intervals normally used by the prescribing physician (estimation: ≥ 6 to ≤ 12 weeks), or until patient death, withdrawal or loss to follow-up, or if significant changes in a patient’s disease are observed. All data will be verified through spot site monitoring, which will take place at up to 10% of all sites involved in the study. An overview of the visit schedule and data collected at each visit is shown in Figure 3. Study end-points are summarised in Figure 4. All adverse events (AEs) will be graded according to the National Cancer Institute Common Terminology Criteria version 3.0 (National Cancer Institute, Bethesda, MD, USA), and their likely relationship to sorafenib therapy will be documented. Tumour assessments will be made by computed tomography or other equivalent radiographical method and will be evaluated using the Response Evaluation Criteria in Solid Tumors.

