**Figure 3 fig03:**
[figure not shown]
GIDEON patient assessment schedule

The population of patients who entered this study and received at least one dose of sorafenib will be valid for intent-to-treat safety and efficacy analysis. However, patients who received sorafenib in the past will be excluded from efficacy analysis. All baseline demographic data will be summarised for the intent-to-treat population. AEs and other safety parameters, including blood pressure, Child-Pugh grade and Eastern Cooperative Oncology Group performance status (ECOG PS), will be summarised using the safety population.

Planned subgroup analyses conducted globally, regionally and by country will include: the impact of baseline characteristics on safety, particularly Child-Pugh B; the relationship between baseline characteristics and efficacy; the duration of sorafenib therapy and reasons for discontinuation; the effect of other treatments for HCC on outcome and the impact of different practice patterns on outcome. In addition, subgroup analyses for specific regions may be conducted, such as: an evaluation of common treatments for HCC in Asia; referral and diagnostic patterns in Europe; duration of treatment, tolerability and compliance in Latin America and patient selection for loco-regional therapy in Japan. However, all subgroup analyses performed will depend on the actual data collected.

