### Statistical considerations for GIDEON

An overall sample size of 3000 patients with unresectable HCC treated with sorafenib is expected to be sufficient to allow for evaluation of safety of the overall population as well as specific subgroups. With this sample size, there would be an 84% chance of observing an AE with a true incidence of 1% in at least 25 patients.

All baseline, safety and efficacy data were analysed using descriptive statistics. Kaplan–Meier estimates were calculated for the OS, PFS and TTP efficacy end-points. At the time of the analyses, any patient alive or lost to follow-up, without disease progression or death or without documented radiological progression will be censored at the last date of evaluation for OS, PFS and TTP analyses, respectively. Exploratory subgroup analyses of efficacy and safety data may also be performed, stratified by prognostic/predictive baseline factors such as stage, Child-Pugh score, ECOG PS, region and age, as appropriate. Data regarding administration of sorafenib such as duration, given dose, continuation or discontinuation of therapy and dose modification of sorafenib therapy, including reason(s) for discontinuation, will be summarised in a descriptive manner. Treatments for HCC other than sorafenib before, during and after therapy with sorafenib will be summarised descriptively as per available data. The sample size was calculated to collect data to allow for sufficient evaluation of safety monitoring of all treated patients. Interim analyses are planned during the study primarily for summarising and monitoring safety data, and will be conducted after 500 patients and 1500 patients are enrolled and have been treated on study for at least 4 months.

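### TTP and, less so, PFS compared by region, country or practice pattern will partly reflect how often tumours are assessed, because assessment timing follows local practice

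*Protocol article*

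**What the plan says.** All places are in the Protocol article.

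- **Aims, objectives and rationale for GIDEON:** in studies of this type, "no additional diagnostic or monitoring interventions are mandated for the patient as a result of inclusion in an NIS".
- **Data collection, timing:** after study entry and the start of sorafenib, data are collected "then at intervals normally used by the prescribing physician" ("estimation: ≥ 6 to ≤ 12 weeks"). The same sentence adds collection "or if significant changes in a patient’s disease are observed".
- **Data collection, tumour status:** "Tumour assessments will be made by computed tomography or other equivalent radiographical method", evaluated by RECIST. The text gives no separate imaging interval. The assessment schedule is in Figure 3, which is not available here.
- **Data collection, subgroup paragraph after Figure 3:** subgroup analyses are planned globally, regionally and by country. They cover baseline characteristics against efficacy and "the impact of different practice patterns on outcome".
- **Statistical considerations for GIDEON:** "Kaplan–Meier estimates were calculated for the OS, PFS and TTP efficacy end-points". Patients without the event are censored at their last evaluation. Efficacy may also be explored by baseline factors that include region.
- **What are the limitations of GIDEON?** This section covers lack of randomisation, control and blinding, small subgroups, patient selection and data quality. It does not mention assessment timing that differs between groups.

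**The concern.** Progression happens at some time between two assessments but enters an ordinary Kaplan–Meier curve at the later one. The average delay is roughly half the assessment interval. Within one cohort this is a familiar feature of the endpoint. Between groups it matters when the interval differs, and here the interval is left to local practice, with a twofold range by the article's own estimate.

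The planned groupings are those along which practice is likely to vary: region, country and practice pattern. In the last of these, look frequency is part of the exposure being studied, so the exposure shifts the endpoint mechanically. Physicians who assess less often would appear to achieve longer TTP on sorafenib. The article wants regional and practice differences to inform treatment decisions, so such a difference could be read as a real effect of region or practice.

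TTP is the most exposed endpoint. PFS is less so, because deaths are dated independently of assessments. OS is unaffected.

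**Working it through.** **The article's own figure.** The article gives no figure for progression. Its one design figure, an 84% chance of seeing a 1% adverse event in at least 25 of 3000 patients, reproduces: the exact binomial probability of 25 or more is 0.844. This point does not depend on it.

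**Inputs.** The intervals D = 6 and D = 12 weeks come from Data collection. The true median times to progression of 3, 4 and 5.5 months are assumptions, because the article gives none. Progression is taken as exponential and identical in both groups.

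**Formula.** With rate λ = ln 2 / median, and progression recorded at the first assessment after it occurs:

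- mean detected TTP = D / (1 − exp(−λD))
- mean delay = mean detected TTP − 1/λ
- apparent rate ratio, 6-week over 12-week group = mean detected TTP at 12 weeks / mean detected TTP at 6 weeks

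**Example, true median 3 months (13.0 weeks).** λ = 0.05332 per week, so 1/λ = 18.76 weeks.

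- 6 weeks: 6 / 0.2738 = 21.91, a delay of 3.16 weeks.
- 12 weeks: 12 / 0.4726 = 25.39, a delay of 6.64 weeks.
- Gap 3.48 weeks; ratio 25.39 / 21.91 = 1.16, where the truth is 1.

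| True median (months) | Mean detected TTP, 6-week (weeks) | Mean detected TTP, 12-week (weeks) | Gap (weeks) | Gap (months) | Rate ratio |
|---|---|---|---|---|---|
| 3 | 21.91 | 25.39 | 3.48 | 0.80 | 1.16 |
| 4 | 28.13 | 31.48 | 3.36 | 0.77 | 1.12 |
| 5.5 | 37.47 | 40.73 | 3.26 | 0.75 | 1.09 |

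**Deaths.** Simulation with ±15% jitter in spacing, and exponential deaths at the article's sorafenib median OS values (6.5 and 10.7 months), gives PFS rate ratios of 1.08 to 1.15.

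**Off-schedule detection.** If a share q of progressions is dated when it occurs, the mean TTP gap shrinks by the factor (1 − q). For a true median of 4 months, simulation gives 0.78 months at q = 0, then 0.58 at 25%, 0.39 at 50% and 0.19 at 75%. The values of q are assumptions.

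**Mixed intervals.** Suppose one third of patients in one group and two thirds in the other are on 12 weeks (an assumption). The gap is then (2/3 − 1/3) of the tabulated value: 3.36 / 3 = 1.12 weeks for a true median of 4 months. The rate ratio is (28.13/3 + 2 × 31.48/3) / (2 × 28.13/3 + 31.48/3) = 30.36 / 29.25 = 1.04.

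**Why medians do not size this.** Detected times cluster at assessments, so an apparent median can jump by a whole interval. A true median of 5.5 months is 23.8 weeks, next to the 24-week assessment. There the apparent median of a 12-week group can land near 25 or near 35 weeks on small changes in timing. The mean gap and the rate ratio are stable.

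**The case against.** The strongest case against has five parts.

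1. **Detection is not confined to routine visits.** This stands. The article also provides for collection on significant disease change, which reduces the artefact. It does not remove it, and how early a change is noticed and imaged also depends on local practice.
2. **A clean 6-versus-12-week split is extreme.** This stands. Nothing in the article says that any region sits wholly at one end, and the range is an estimate for data collection rather than imaging. The table is therefore an upper bound for that range, not a forecast.
3. **The analyses are descriptive, and stratified efficacy is exploratory.** This stands in part. The practice-pattern analysis refers to outcome without naming PFS or TTP. A reader might infer that false significant regional differences are to be expected, but the article plans no significance test, so a false-positive rate would describe a procedure that it does not propose. A displayed difference between curves can still mislead without a test.
4. **Free spacing is inherent to a non-interventional study, and the full analysis plan may deal with it.** The first half is right: the weakness lies in the comparison, not in failing to fix visits. On the second, the article does state a method, a censoring rule and a set of comparisons, and that combination has this consequence as written.
5. **The article already urges caution on efficacy.** It does, and it calls for results to be read with randomised trials. Its cautions do not cover unequal assessment timing, which distorts comparisons within the study itself.

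**Conclusion.** The point holds in limited form. As described, comparisons of TTP and, to a lesser degree, PFS by region, country or practice pattern mix disease course with assessment frequency, and the limitations section does not say so.

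Within the 6-to-12-week range, the distortion in mean detected TTP is at most about 3 to 3.5 weeks, with a rate ratio of about 1.09 to 1.16. This assumes exponential progression with a true median of 3 to 5.5 months, a complete split between groups, and no off-schedule detection. Realistic mixing or off-schedule detection makes it smaller, and the article does not allow the actual size to be fixed.

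A reader might also infer that the efficacy results as a whole are unsound. The documents do not support that. Safety is the primary objective, OS is untouched, and Kaplan–Meier for the overall cohort is conventional if read as time to detected progression.

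**What to change.** For comparisons of TTP and PFS by region, country or practice pattern:

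- Report the observed interval between tumour assessments in each group beside the estimates.
- Add an analysis that treats progression as interval-censored between the last progression-free assessment and the one showing progression (for example a Turnbull estimate or an interval-censored Weibull model). Date deaths in PFS exactly.
- Interpret any TTP or PFS difference alongside OS.
- Keep ordinary Kaplan–Meier for the overall cohort, labelled as time to detected progression.
- Add unequal assessment timing to the stated limitations.

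No visit, imaging or treatment practice changes. The cost is some added programming, wider intervals and a less familiar estimate. The fix relies on assessment dates being recorded. The censoring rule, which uses the last evaluation date, implies this, but the article does not state it outright.
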